#### FUNDING AND SUPPORT IN KIND

|                                                                                                                              |                                                |
|------------------------------------------------------------------------------------------------------------------------------|------------------------------------------------|
| FUNDER(S)
(Names and contact details of ALL organisations providing funding and/or support in kind for this trial) | The Health Foundation (£ 74,920.06)            |
|                                                                                                                              | CyberLiver (manufacturing costs of the device) |

[figure not shown]

## ROLE OF STUDY SPONSOR AND FUNDER

The sponsor for this study is UCL. The role of the sponsor is to ensure arrangements are provided for initiation, management and monitoring of the study. The sponsor will also ensure that an appropriate research ethics committee has reviewed the study and provided a favourable opinion, and that arrangements proposed for the work are consistent with this research governance framework.

The funder of this study is The Health Foundation and CyberLiver (manufacturer).

Neither the sponsor, nor the external funder, have any role in the trial design, data analysis, interpretation, manuscript preparation or dissemination.

## ROLES AND RESPONSIBILITIES OF TRIAL MANAGEMENT COMMITTEES/GROUPS & INDIVIDUALS

Since this a small, single-centre pilot study, a Trial Management Committee will not be involved. However, patient involvement has been sought in the design of this study, with active engagement with Camden Alcohol Users Group to identify patient-reported outcomes that are assessed in the questionnaire data in the trial design. Day to day management of the study will remain the responsibility of the CI and the PIs.

The ethics application and submission and development of informed consent documents will be undertaken by an independent contract research organisation PHARMExcel Ltd.

Monitoring will also be performed by Pharmexcel Ltd, at a single time point during the study period.

### Protocol contributors:

The protocol has been developed by [name], [name] and [name]. The Protocol has been reviewed by The Health Foundation as part of the funding review process, and UCL R&D department as part of the sponsorship process.

### KEY WORDS:

Alcoholic liver disease  
Alcohol  
Smartphone  
Digital health  
Behaviour change

[figure not shown]

[figure not shown]

## LIST OF ABBREVIATIONS

|         |                                                                                                                        |
|---------|------------------------------------------------------------------------------------------------------------------------|
| AE      | Adverse Event                                                                                                          |
| ALD     | Alcohol Liver Disease                                                                                                  |
| AR      | Adverse Reaction                                                                                                       |
| BCI     | Behaviour Change Interventions                                                                                         |
| CA      | Competent Authority                                                                                                    |
| CI      | Chief Investigator                                                                                                     |
| CRF     | Case Report Form                                                                                                       |
| CRO     | Contract Research Organisation                                                                                         |
| EC      | European Commission                                                                                                    |
| EMA     | European Medicines Agency                                                                                              |
| EU      | European Union                                                                                                         |
| GCP     | Good Clinical Practice                                                                                                 |
| HES     | Hospital Episode Statistics                                                                                            |
| HRQoL   | Health-Related Quality of Life Questionnaire                                                                           |
| ICF     | Informed Consent Form                                                                                                  |
| ICH     | International Conference on Harmonisation of technical requirements for registration of pharmaceuticals for human use. |
| ISF     | Investigator Site File                                                                                                 |
| ISRCTN  | International Standard Randomised Controlled Trials Number                                                             |
| IVD     | In vitro diagnostic                                                                                             |
| IVDD    | In vitro diagnostic Directive                                                                                   |
| MHRA    | Medicines and Healthcare products Regulatory Agency                                                                    |
| MDD     | Medical Device Directive                                                                                               |
| MS      | Member State                                                                                                           |
| NHS R&D | National Health Service Research & Development                                                                         |
| PI      | Principal Investigator                                                                                                 |
| PIC     | Participant Identification Centre                                                                                      |
| PIS     | Participant Information Sheet                                                                                          |

[figure not shown]

|       |                                               |
|-------|-----------------------------------------------|
| QA    | Quality Assurance                             |
| QC    | Quality Control                               |
| RCT   | Randomised Control Trial                      |
| REC   | Research Ethics Committee                     |
| RFH   | Royal Free Hospital                           |
| SAE   | Serious Adverse Event                         |
| SOC   | Standard of Care                              |
| SAR   | Serious Adverse Reaction                      |
| SDV   | Source Data Verification                      |
| SOP   | Standard Operating Procedure                  |
| SSI   | Site Specific Information                     |
| SUSAR | Suspected Unexpected Serious Adverse Reaction |
| TLFB  | Time Line Follow Back Method                  |
| TMG   | Trial Management Group                        |
| TSC   | Trial Steering Committee                      |
| TMF   | Trial Master File                             |
| UCL   | University College London                     |
| UNC   | University of North Carolina                  |

[figure not shown]

## TRIAL FLOW CHART

### 1. Patient Flow

[figure not shown]

### 2. AlcoChange messaging flowchart

[figure not shown][figure not shown]

## STUDY PROTOCOL

## AlcoChange: An Open Label Pilot Study of Smartphone Monitoring for Alcoholic Liver Disease

## 1 BACKGROUND

Alcohol misuse is a common cause of morbidity and mortality in the UK, accounting for more premature deaths amongst individuals of working age than cigarette smoking. It is estimated that 24% of the UK adult population drink at harmful levels, but only 6% of these receive any input from alcohol services. Abstinence leads to markedly improved outcomes in patients with alcoholic liver disease (ALD) - continued drinking following diagnosis leads to ~50% mortality at 3 years, whereas with abstinence >75% are alive at 7 years. Thus, **any intervention that decreases alcohol use and improves abstinence will improve mortality in this group**. Currently, there is no provision of high-intensity alcohol support for patients discharged with ALD, despite their high mortality.

**Behaviour change interventions (BCIs) are effective tools for reducing alcohol consumption.** Behaviour change interventions (BCIs) are effective at reducing alcohol consumption in targeted individuals, and have been the subject of over 20 randomised clinical trials (RCTs), and a Cochrane review(1). The most important aspect of a BCI that leads to decreased alcohol use is **self-monitoring of alcohol intake**. Thus, from systematic review, self-monitoring of alcohol is the single key technique that significantly predicts success of a brief intervention (1).

The aim of this pilot study is to provide 60 ALD patients with the AlcoChange device, to enable accurate self-monitoring of alcohol use, and determine changes in self-reported alcohol use over the study period.

1. Michie S et al. Identification of behaviour change techniques to reduce excessive alcohol consumption. *Addiction* 2012;107(8):1431-40.

## 2 RATIONALE

Mobile phone technology has been previously demonstrated to change health behaviours - text messaging has been successfully used to reduce cigarette smoking(1). However, smartphones have not previously been used to facilitate BCIs in ALD, or to facilitate self-monitoring in any population with alcohol misuse.

The hypothesis of this study is that use of the AlcoChange device, according to the functionality outlined above in figure 2, will lead to a >20% reduction in self-reported alcohol intake, or a maintenance of abstinence, over a 3-month period in patients with ALD.

[figure not shown]

Since this is a pilot study, the study design is open-label, single-arm with no control group. Compliance with the device, as well as patient reported outcomes, quality of life and patient empowerment scores will be important secondary endpoints. A further endpoint will be qualitative assessment by focus group to explore: (i) facilitating factors and barriers to use of the app, and (ii) factors which influenced drinking behaviour in the study cohort.

Additionally, this study will incorporate tertiary, exploratory endpoints to address the role of oral health, and oral and gut microbes, in the natural history of ALD. A baseline dental examination will be performed, and baseline samples of saliva and stool will be collected to determine microbial populations. Saliva and stool samples will also be collected at the end of study visit, to determine changes in oral and gut microbe populations with decreased alcohol use. Data on hospital re-admission will be obtained from hospital episode statistics (HES) data to determine if baseline dentition or oral/gut bacterial populations predict re-admission in ALD.

1. Free C et al. Smoking cessation support delivered via mobile phone text messaging (txt2stop): a single-blind, randomised trial. *Lancet* 2011;378:49-55

## 2.1 Assessment and management of risk

This study does not alter the standard of care (SOC) of patients admitted with ALD. The only intervention is a smartphone application and breathalyser (device), which has been CE marked as an *in vitro* diagnostic medical device, and hence the risks involved are minimal compared to SOC and are likely to minimise harm.

### Key Risks and Mitigation

The main risks involved in the study and their respective mitigation are as follows,

#### 1. False positives breathalyser readings

In remote cases, it is possible that presence of alcohol is shown when in reality the user has not consumed any alcohol. The reasons for this could be ethanol residues from previous tests, ethanol generated by the human body, or consumption of cough syrups. In such cases, the risk will be managed through education and training. Users know that they have not consumed alcohol and will be informed that repeated tests can flush out accurate results.

#### 2. False negative breathalyser readings

In remote cases, it is possible that while the user has alcohol present in their blood, the reading may be displayed as nil. The reason for this may be due to inaccurate breath sampling (breath from the mouth as opposed to the lungs of the user). This risk will be mitigated through provision of appropriate risk messages (see below) even when the readings are nil.

### Warnings on Drinking and Driving

Users will be strictly told not to drive after consuming any amount of alcohol. The message will be propagated in various sections of AlcoChange app where relevant as well as in a printed format along with the Breathalyser hardware.

**The following message will be shown in the “About Us” screen in the app:**

[figure not shown]

“Warning:

AlcoChange is not intended to be a medical device. You should consult a qualified medical professional for all matters concerning your health. AlcoChange cannot be held responsible for any actions by the user.”

**The following message will be shown in the breathalyser results screen:**

“It is an offence to drive or perform any activity that may require you to be alert after consuming an alcoholic beverage, whatever the level of alcohol in the blood. Please note that the level of alcohol is not easily translated into the number of drinks you have had, since this depends on a variety of factors including gender, height, weight, stomach emptiness, type of drink and others. Any amount of alcohol will affect your ability to drive. Therefore it is best to never drink and drive. If you drive after a drink, you could be prosecuted and possibly convicted.”

### 3 OBJECTIVES AND OUTCOME MEASURES/ENDPOINTS

#### 3.1 Primary objective / outcome measures

The primary objective is to determine the effect of use of the AlcoChange device on self-reported alcohol use at 3 months, amongst patients with ALD. The hypothesis is that use of the AlcoChange device will lead to a >20% reduction in self-reported alcohol use at 3 months.

The outcome measure of alcohol intake within the preceding 3 months will be assessed by the timeline follow-back method, which is a commonly used endpoint in alcohol intervention studies. This will be assessed by paired t-test or Wilcoxon signed-rank test.

The initial interview will be conducted in either the inpatient or outpatient setting, after the patient has been screened and consented for entry into the study. The second interview will be conducted in the outpatient setting, at the time of the patient’s follow-up appointment at 3 months (between 10-14 weeks, as part of SOC).

#### 3.2 Secondary objectives / outcome measures

The secondary objectives will assess compliance with the AlcoChange device, attendance at community alcohol services, and assessment of health related quality of life (HRQoL) and patient empowerment.

Compliance with the AlcoChange device will be assessed by quantifying the number of interactions with the device by the patient over the 3-month study period.

Attendance at community alcohol services following discharge from hospital will be assessed by direct contact with the community alcohol centre at the end of the study period (list of community

---

 Note the research team will contact the community alcohol services directly at the end of the study to gather information on community attendances. The community services will not have any involvement in the study or any access to study information.

[figure not shown]

alcohol centres attached). Current non-attendance rates following discharge from hospital are ~50%.

Health-related quality of life (HRQoL) and patient empowerment will be assessed by questionnaires, which will be administered at baseline and at the end of study follow-up appointment at 3 months. The SF-36 questionnaire will be used to assess HRQoL, and patient empowerment will be assessed by the SUSTAINS questionnaire which is designed and validated to assess the impact of e-health interventions on patient empowerment and relationship with health services.

Qualitative research methodologies will also be used in order to gain deeper understanding of facilitating factors and barriers to use of the app, and factors which influence drinking behaviour. Study participants will be contacted by telephone, and asked for their willingness to participate in a focus group to explore the above issues. Two focus groups will be conducted, with four to six participants in each group. Each will last up to one hour and a half. A topic guide will be developed to direct the focus groups. Participants will be asked for their thoughts about facilitators and barriers to use of the AlcoChange app, and factors that influenced changes in drinking behaviour. Specific interactions between use of the app and factors that influenced changes in drinking behaviour. Specific interactions between use of the app and changes in drinking behaviour will be explored.

### 3.3 Exploratory endpoints/outcomes

There is increasing interest in the role of oral and gut microbes in the natural history of liver disease. Additionally, periodontal disease has been associated with adverse health outcomes in diabetes mellitus and coronary heart disease, through effects of endothelial function. Importantly, endothelial dysfunction is a key component of the development of complications of cirrhosis.

The hypothesis of this part of the study is that the presence of periodontitis, or the baseline oral and gut bacterial populations, will be associated with outcomes from liver disease with one year. No individual patient data will be acquired beyond the 3-month study period, but re-admission will be obtained from Hospital Episode Statistics. Additionally, the effect of reduced alcohol intake from baseline on oral and gut microbes will be assessed, by repeat saliva and stool sampling at 3-months.

The presence of periodontitis will be assessed by dental examination, which will be conducted during the patient's inpatient stay. This will include a basic periodontal examination which should not exceed 15 min in duration. Using a manual University of North Carolina (UNC-15) periodontal probe, the tip of the probe is gently inserted into the gingival pocket and the depth of insertion measured in millimetres on the probe. Probing force should not exceed 20-25 gm. Further details of the dental examination are attached.

| Objectives        | Outcome Measures                  | Timepoint(s) of evaluation of this outcome measure (if applicable) |
|-------------------|-----------------------------------|--------------------------------------------------------------------|
| Primary Objective | Self-reported alcohol intake will | Self-reported alcohol intake will                                  |

[figure not shown]

|                                                                                                                                                                                                                                                                                                                                                                                                                                                                                                 |                                                                                                                                                                                                                                                                                                                                                                                                                                                                                                                                                               |                                                                                                                                                                                                                                                                                                                                                                                                                                                                                                                                                         |
|-------------------------------------------------------------------------------------------------------------------------------------------------------------------------------------------------------------------------------------------------------------------------------------------------------------------------------------------------------------------------------------------------------------------------------------------------------------------------------------------------|---------------------------------------------------------------------------------------------------------------------------------------------------------------------------------------------------------------------------------------------------------------------------------------------------------------------------------------------------------------------------------------------------------------------------------------------------------------------------------------------------------------------------------------------------------------|---------------------------------------------------------------------------------------------------------------------------------------------------------------------------------------------------------------------------------------------------------------------------------------------------------------------------------------------------------------------------------------------------------------------------------------------------------------------------------------------------------------------------------------------------------|
| 
 
- To compare self-reported alcohol intake amongst patients with ALD, following 3 months of use of the AlcoChange device.
 
                                                                                                                                                                                                                                                                                                                      | 
be assessed at baseline and at 3 months by the timeline follow back method. Self-reported alcohol intake will be assessed for the preceding 3 months at both time points.
                                                                                                                                                                                                                                                                                                                                                                              | 
be assessed at baseline, as an inpatient, and again at the end of study visit at 3 months (10-14 weeks).
                                                                                                                                                                                                                                                                                                                                                                                                                                         |
| 
Secondary Objectives
 
 
- To assess compliance with the AlcoChange device.
 
- To assess attendance at community alcohol services following discharge.
 
- To assess changes in health related quality of life (HRQoL) during the study period.
 
- To assess changes in patient empowerment during the study period.
 
- Factors determining compliance with the app and effect on drinking behaviour
 
 | 
 
- Compliance will be assessed by analysing the number of interactions with the device over the study period.
 
- Follow-up rates at community alcohol services appointments over the study period will be assessed.
 
- HRQoL will be assessed by SF-36 questionnaire before and after the study period.
 
- Patient empowerment will be assessed by SUSTAINS questionnaire before and after the study period.
 
- Qualitative analysis by focus group of up to 12 participants
 
 | 
 
- Compliance will be recorded by the AlcoChange platform throughout the study period.
 
- Attendance at community alcohol follow-up will be assessed by direct contact with the community alcohol centre at the end of the study period.
 
- Questionnaires for HRQoL and patient empowerment will be assessed at baseline, as an inpatient, and again at the end of study visit at 3 months (10-14 weeks).
 
- Following completion of the 3 months period of use of AlcoChange
 
 |
| 
Tertiary Objectives
 
 
- To determine the prevalence of periodontitis amongst patients with ALD.
 
- To determine changes oral and gut microbial populations over the study period.
 
- To determine if the presence of periodontitis or saliva/stool microbial populations are related to frequency of hospital admissions up to 1 year.
 
                                                                            | 
 
- The presence of periodontitis will be determined by dental examination at baseline.
 
- Microbial populations in saliva and stool will be determined at baseline and at the end of the study period.
 
- The presence of periodontitis and microbial populations in saliva and stool will be correlated with frequency and type of readmission with liver disease up to 1 year.
 
                                                                                                             | 
 
- Dental examination will be conducted at baseline, as an inpatient.
 
- Saliva and stool sampling will be conducted at baseline, as an inpatient, and again at the end of study visit at 3 months (10-14 weeks).
 
- Data on readmissions at 1 year will be obtained from Hospital Episode Statistics.
 
                                                                                                                                                                                 |

[figure not shown]

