## 6 TRIAL PROCEDURES

**Table 1 Schedule of Assessments**

|                                                          | Inpatient/ Outpatient | Outpatient          | Outpatient  |
|----------------------------------------------------------|-----------------------|---------------------|-------------|
|                                                          | Screening/Baseline    | 3 months (10-14wks) | 14-52 weeks |
| Informed Consent                                         | *                     |                     |             |
| Demographics                                             | *                     |                     |             |
| Past medical history                                     | *                     |                     |             |
| Concomitant medication                                   | *                     |                     |             |
| QOL questionnaire SF36                                   | *                     | *                   |             |
| Patient empowerment questionnaire (SUSTAINS)             | *                     | *                   |             |
| Dental examination                                       | *                     |                     |             |
| Stool Sample                                             | *                     | *                   |             |
| Saliva Sample                                            | *                     | *                   |             |
| Routine Biochemistry and Haematology blood samples (SOC) | *                     | *                   |             |
| Adverse Events                                           | *                     | *                   |             |
| Provide device                                           | *                     |                     |             |
| Focus group assessment (up to 12 participants)           | *                     |                     | *           |

[figure not shown]

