## **6.3 Baseline data**

The baseline data set to be collected is:

- Age
- Gender
- Ethnicity
- Postcode
- Possession of smartphone and type of smartphone
- Previous 3 months of alcohol intake (by timeline follow back method)
- Quality of life questionnaire (SF36)
- Patient empowerment questionnaire (SUSTAINS)

Blood tests will be performed as SOC. The results of these tests will also be accessed by the research team and data collected on the following variables:

- Cabohydrate deficient transferrin
- Routine haematology and biochemistry

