### 6.5 Long term follow-up assessments

There will be follow-up of participants beyond the 3-month study period. Data on hospital admissions up to 1 year will be assessed by accessing Hospital Episode Statistics data.

Patients that do not attend a follow-up clinic visit between 10-14 weeks will be contacted by telephone during the period 14-16 weeks following recruitment, to make arrangements to conduct the interview regarding alcohol consumption over the preceding 3 months (either in person or by telephone). If the patient cannot be contacted by week 16, then no further attempts to contact the patient by telephone will be made.

In case of premature discontinuation, similarly the research team will attempt to contact the patient by telephone within 14 days after discontinuation, to conduct the alcohol consumption interview. In this case, statistical analysis will be conducted by the Last Observation Carried Forward method.

Patients who complete the above assessments may be contacted up to 52 weeks following inclusion, to ask willingness to participate in a focus group (up to 12 participants, as described in 3.2 above).

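### The 3-month recall at a follow-up visit allowed from week 10 counts up to 3 weeks of pre-device drinking as on-device intake

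*Combined protocol and SAP*

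**What the plan says.** Section 3.1 defines the primary outcome: "The outcome measure of alcohol intake within the preceding 3 months will be assessed by the timeline follow-back method". The objectives table in section 3.3 applies the same look-back twice: "Self-reported alcohol intake will be assessed for the preceding 3 months at both time points". Section 6.3 lists the baseline item as "Previous 3 months of alcohol intake (by timeline follow back method".

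In Table 1, the row "Provide device" is marked in the screening/baseline column only, so use of the device starts where the baseline recall ends. Section 3.1 places the second interview "at the time of the patient’s follow-up appointment at 3 months (between 10-14 weeks, as part of SOC". Under section 6.5, patients who miss that visit "will be contacted by telephone during the period 14-16 weeks following recruitment". Those who stop prematurely are telephoned within 14 days of stopping for the same alcohol interview, and no shorter recall period is given for them.

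The stated expectation is: "The hypothesis is that use of the AlcoChange device will lead to a >20% reduction in self-reported alcohol use at 3 months". Sections 3.1 and 9 name a paired t-test or Wilcoxon signed-rank test. No section limits follow-up recall to days since device supply, removes days already counted at baseline, or adjusts for the week of the visit.

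**The concern.** The objective in section 3.3 is intake after 3 months of device use. A look-back of about 13 weeks from a visit at week 10, 11 or 12 reaches back past device supply into days that the baseline interview has already counted. For those participants the follow-up value mixes on-device and pre-device drinking, and the two paired measurements partly share the same data. The size of the mixture depends on the clinic date.

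The estimated change is meant to inform the feasibility of a randomised trial (section 4). A distortion that varies with appointment date and with drinking just before enrolment is hard for a reader to correct afterwards.

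**Working it through.** The plan gives no calculation on this point and section 9 states that no formal sample size calculation was done, so there is no figure to reproduce. The check is direct arithmetic.

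**Inputs**
- Look-back L: 3 months at both interviews (sections 3.1, 3.3, 6.3). L = 13 weeks, or L = 12 if a month is read as 4 weeks.
- Visit week t: 10 to 14 (sections 3.1, 3.3).
- Device supplied at baseline (Table 1), taken as week 0.
- Hypothesised reduction r = 20% (section 3.1).

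**Formulas.** Overlap o = max(0, L − t). Let B be the mean baseline intake. Assume the o overlapping weeks were drunk at rate B and that the effect r is constant from supply. Mean follow-up intake is then [oB + (L − o)B(1 − r)]/L, so

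observed reduction = r × (1 − o/L).

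**By visit week, true reduction 20%**

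| Visit week | Overlap, L = 13 | Observed, L = 13 | Overlap, L = 12 | Observed, L = 12 |
|---|---|---|---|---|
| 10 | 3 (23%) | 15.4% | 2 (17%) | 16.7% |
| 11 | 2 (15%) | 16.9% | 1 (8%) | 18.3% |
| 12 | 1 (8%) | 18.5% | 0 | 20% |
| 13–14 | 0 | 20% | 0 | 20% |

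To show 20% at week 10, the true reduction must be 20/(10/13) = 26%, or 20/(10/12) = 24% with L = 12.

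**Average over visits.** The documents do not give the spread of visit dates. If visits are uniform over weeks 10 to 14:
- L = 13: mean overlap = (3²/2)/4 = 1.125 weeks; observed = 20 × (1 − 1.125/13) = 18.3%.
- L = 12: mean overlap = (2²/2)/4 = 0.5 weeks; observed = 20 × (1 − 0.5/12) = 19.2%.

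**Dry days just before baseline.** Section 5.1 admits dependent patients after inpatient detox, so the last days before baseline may be dry. The documents give no number of days, so d is varied. Take L = 13, a week-10 visit and B = 1. Drinking on the remaining baseline days then runs at 13/(13 − d/7), and the 3 overlapping weeks contribute (3 − d/7) × 13/(13 − d/7). Observed reduction = 1 − [10(1 − r) + that contribution]/13.

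| Dry days d | Contribution of overlap | Observed, true 20% | Observed, true 50% |
|---|---|---|---|
| 0 | 3.00 | 15.4% | 38.5% |
| 5 | 2.42 | 19.9% | 42.9% |
| 7 | 2.17 | 21.8% | 44.9% |
| 14 | 1.18 | 29.4% | 52.4% |

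About 5 dry days cancel the dilution of a true 20% effect, and 7 reverse it. A larger true effect needs more dry days before it reverses.

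**Early discontinuation.** If the same 3-month recall is used, a patient who stops at week 4 and is telephoned at week 6 has 13 − 6 = 7 overlapping weeks (54%). A 20% reduction sustained to the call reads as 20 × 6/13 = 9.2%, with no dry days. Section 6.5 specifies last observation carried forward for this case, so such a value could stand as the 3-month outcome.

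**The case against.** Four points can be made against this, and each limits the claim.

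- **Size.** A reader might infer that the trial loses 23% of its effect. That is the earliest permitted visit only. There is no overlap from week 13, nor in the calls at weeks 14 to 16, and the average under uniform visits is about 18.3% for a true 20%. The label in Table S4 for abstinence at week 12 of therapy suggests the 12-week reading, which gives 19.2%. This stands: average dilution among planned attenders is modest.
- **Direction.** A reader might infer that the effect is always pulled towards zero. The documents do not support that, because section 5.1 admits patients after detox and the objectives table describes baseline as an inpatient assessment. This stands: the direction is uncertain for them.
- **The 20% figure.** A reader might infer that the overlap could make the trial fail a formal 20% criterion. Sections 3.1 and 9 give no test against 20% and no success rule at 20%; the named tests are of change from zero. Section 2 also allows maintained abstinence as an alternative, and someone abstinent throughout both windows is unaffected. This stands: the overlap affects how the estimate reads against the hypothesis, and no decision rule is broken.
- **Reported results.** Table S4 gives an overall median change of −75.49%, with one quartile at −100%. Anyone with pre-device drinking inside the follow-up window could not reach −100%. The table does not state its recall window, so it does not show that overlap was avoided in general. It does show a median far from 20%.

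None of these removes the overlap from the written definition.

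**Conclusion.** The point holds in a limited form. Followed as written, the plan counts pre-device days as on-device intake for any interview before about week 13, by up to 3 of 13 weeks (2 of 12 on the shorter reading). That rests only on the plan's own windows and on device supply at baseline.

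The effect on the estimate rests on assumptions. With drinking at the average rate up to supply and a constant effect afterwards, a true 20% reads as 15.4% at week 10 and 18.5% at week 12. Averages of 18.3% and 19.2% further assume evenly spread visits. The bias is towards zero for participants drinking up to baseline. It can cancel or reverse where the days before baseline were dry. The largest overlap would fall on early discontinuers, for whom section 6.5 states no window.

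This should be fixed because it concerns the definition of the primary outcome and the repair is nearly free. It does not invalidate an uncontrolled pilot.

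**What to change.** In sections 3.1, 3.3 and 6.5, define follow-up intake as mean g/week over the days from device supply to the interview, going back at most 3 months and never including days before supply. State that the same rule applies to interviews after early discontinuation. Keep baseline as mean g/week over the 3 months before enrolment, and state that unit in section 6.3. Under this rule the overlap is zero at every visit week, so a constant true 20% reduction reads as 20%.

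Handling of inpatient days can be a sensitivity analysis. Excluding them from the main analysis would change what is being estimated, and the documents give no lengths of stay from which to judge the effect.

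The cost is wording in these sections and on the interview form, with no extra visit. The downside is a slightly shorter recall window for early attenders: 10 weeks rather than 13 at a week-10 visit. For early discontinuers it can be much shorter. The fix assumes that the timeline follow-back is recorded by day. The documents do not describe the form, so the sponsor should confirm this.
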